Therefore, this study aims to identify clinical, laboratory, echocardiographic and angiographic features that could refine available risk assessment schemes post-AMI. The ultimate goal is to develop a contemporary predictive risk model that includes clinical parameters, angiographic characteristics, biochemical biomarkers of systemic inflammation and echocardiographic myocardial work indices to identify high-risk patients in the acute phase and predict downstream cardiovascular complications.

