## 2. Materials and Methods

### Study Design and Population

The ‘‘CLEAR-AMI’’ (ClinicalTrials.gov Identifier: NCT05791916) is a prospective, investigator-initiated, non-interventional study including patients with first AMI, ST-segment elevation myocardial infarction (STEMI) and Non-ST-segment elevation myocardial infarction (NSTEMI), hospitalized at the First Department of Cardiology of AHEPA University Hospital in Thessaloniki, Greece. All the patients undergo emergency coronary angiography in line with current guidelines [2]. The study adheres to the fundamental guidelines delineated in the Declaration of Helsinki [13] and the rules of good clinical practice, and has been approved by the Ethics Committee of the Aristotle University of Thessaloniki (reference number: 6.582/2022). The whole study design is presented in Figure 1.

This study aims to enroll a consecutive series of 500 patients presenting with first STEMI or NSTEMI and who are undergoing primary or emergency coronary angiography. A written informed consent is provided before enrollment for each eligible patient. Patients with a history of coronary artery disease, previous AMI or previous coronary intervention (percutaneous or surgical) will be excluded. Upon attaining the cohort of 500 patients, subgroup analyses will be conducted for NSTEMI and STEMI patients. The detailed eligibility criteria are described in Table 1.

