Artificial intelligence, specifically machine learning tools such as Extreme Gradient Boosting (XGBoost), will be used to identify clinical laboratory, echocardiographic and angiographic biomarkers with significant prognostic value and create potent diagnostic algorithms and predictive models. XGBoost stands as a prominently employed machine learning technique that is recognized for its exceptional efficacy and various functionalities, including regression, classification, and ranking quandaries [14]. It utilizes an iterative process of recursive binary partitioning to pinpoint the most advantageous division at each step, culminating in the development of an improved model [14].

All eligible patients with AMI will be actively encouraged to participate in a post-myocardial infarction exercise-based cardiac rehabilitation program as recommended by the current guidelines [2]. AMI patients will be encouraged to follow a personalized exercise program consisting of three sessions per week and supervised by a trainer under doctors’ directions. The aerobic and anaerobic exercises selected will be based on the age, gender, and physical status of each patient. The duration will initially be 30 min and the intensity will be low. Both the duration and intensity will be increased gradually according to the patients’ progress, aiming to exercise 5 times per week, 1 h per session with moderate intensity. The maximum heart rate obtained will be based on the stress ECG test that they will have in advance of the rehabilitation at 1 month post-AMI.

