### 3.2. Statistical Analysis

The baseline clinical, echocardiographic, laboratory and angiographic features will be examined and compared by the chi-square test for categorical variables for each group. Student’s t-test, or the analysis of variance (ANOVA) will be used for continuous variables. When assumptions of normality are not met, non-parametric tests (Mann–Whitney U, Wilcoxon etc.) will be performed. Continuous variables will be represented by mean ± standard deviation (SD) or median (1st–3rd quartile). Categorical variables will be summarized by frequencies and percentages (%).

Univariable and multivariable logistic regression analyses, and Cox regression analyses will be applied to identify independent predictors at follow-up. Multivariate models will include only the co-variates that are significantly associated with the endpoint at univariate analysis. Receiver operating curves will evaluate the specificity and sensitivity of the resulting echocardiographic, clinical, angiographic and laboratory biomarkers for the prediction of early and late mortality, and rehospitalization. A likelihood ratio test will be used to assess the additional increase in the chi-square value in order to evaluate the potential incremental prognostic value of novel imaging or laboratory parameters over baseline models. To assess the clinical prognosis of several groups of patients with specific echocardiographic or laboratory characteristics, a time-to-event analysis will be performed according to the Kaplan–Meier method. A log-rank test will be used to compare the event rates. The significance threshold for all statistical tests will be considered the two-tailed *p* value of 0.05. The outcomes will be reported with 95% confidence intervals. Data management and statistical analyses will be conducted using SPSS software, version 26 (IBM SPSS Statistics) and R version 3.4.4 (R Foundation for Statistical Computing, Vienna, Austria). 

To calculate the sample size of the study, the G*Power software version 3.1.9.6 was used. It was estimated that to detect an odds ratio > 1.5, approximately 500 patients with AMI will be required with a power of 90%, a statistical significance level < 0.05 and assuming a dropout rate of 20%. The sample size calculations were based on previously published studies on the evaluation of myocardial work indices in patients with AMI [19,20].

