## 5. Limitations

Several limitations of the study should be acknowledged. Despite the prospective character of the study and the meticulous echocardiographic protocol that is followed, its single-centre nature will entail the need for future confirmation of the results from other centres to ensure their clinical validity. Future studies that include other ethnicities and races and investigate the influence of patients’ genetic profiles, aspects which are not examined in the current study, should be conducted to account for the intrinsic diversity across patient cohorts and verify the applicability and universality of our findings.

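### Markers are chosen by univariate significance and then scored by ROC curves in the same 500 patients, with no optimism correction stated, so the regression-based accuracy figures will be too favourable

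*Protocol article*

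**What the plan says.** The Introduction of the Protocol article sets the aim: "The ultimate goal is to develop a contemporary predictive risk model". The patients are a single series at one hospital (Study Design and Population): "This study aims to enroll a consecutive series of 500 patients presenting with first STEMI or NSTEMI". No second cohort is described.

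Section 3.2 then gives two steps in order.

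- Selection: "Multivariate models will include only the co-variates that are significantly associated with the endpoint at univariate analysis".
- Assessment: "Receiver operating curves will evaluate the specificity and sensitivity of the resulting echocardiographic, clinical, angiographic and laboratory biomarkers", for early and late mortality and for rehospitalization.

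Separately, section 3 says that machine-learning tools such as XGBoost "will be used to identify clinical laboratory, echocardiographic and angiographic biomarkers with significant prognostic value and create potent diagnostic algorithms and predictive models". It gives no tuning or assessment method for them.

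On validation, the article has one remark, in section 5: "its single-centre nature will entail the need for future confirmation of the results from other centres to ensure their clinical validity". It does not mention a split sample, cross-validation, bootstrap or calibration, and it does not rule any of them out.

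**The concern.** A marker that passes a significance screen does so partly on true association and partly on chance in this sample. The same chance then raises its AUC when the ROC curve is drawn in the same patients. Refitting the coefficients in those patients adds further optimism. New patients do not share this sample's chance findings, so the figures do not carry over to them.

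This matters because the product of the study is a risk model meant to improve on available scores. Those scores were derived elsewhere, so their AUC in this cohort carries no such inflation. A comparison of a model tuned here with a score not tuned here is tilted towards the new model. A gain of a few hundredths of AUC could come from the optimism alone.

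**Working it through.** **Inputs from the article.** N is about 500, with odds ratio above 1.5, 90% power, two-tailed 0.05 and 20% dropout (section 3.2). The primary endpoint is all-cause mortality (section 3). The event rate and the number of candidate predictors are not given.

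**Candidates named.** Counting sections 3 and 3.1:

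- 10 laboratory markers: hs-cTnT, NT-proBNP, lipoprotein A, apolipoproteins B and A1, hs-CRP, NLR, IL-6, suPAR, glucose
- 6 scores or angiographic items: Killip, GRACE, two TIMI scores, SYNTAX, dominance
- 6 conventional echocardiographic indices: LVEF, E/e', FAC, TAPSE, S', PASP
- 3 chamber strains
- 4 LV and 4 RV work indices

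The total is 10 + 6 + 6 + 3 + 8 = 33, so 20 to 40 is a reasonable range.

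**The plan's own figure.** The article states no AUC. Its sample-size statement, "It was estimated that to detect an odds ratio > 1.5, approximately 500 patients with AMI will be required", can be reached for one standardised continuous predictor with

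n = (1.960 + 1.282)² / [p(1 − p) × ln(1.5)²], then n / (1 − 0.20).

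- p = 0.20: 10.51 / (0.16 × 0.1644) = 400, and 400/0.8 = 500.
- p = 0.10: 711, then 889.
- p = 0.05: 1346, then 1683.

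So 500 is reproduced exactly at an assumed 20% event rate and an odds ratio per SD. Other assumptions come close (one-sided with 15% events gives 512), so this does not show what was planned. I therefore used 5%, 10% and 20%.

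**Events.** In 500 patients these rates give 25, 50 and 100 events. In the 400 left after 20% dropout they give 20, 40 and 80. Over 33 candidates, that is 20/33 = 0.6, 40/33 = 1.2 and 80/33 = 2.4 events per candidate.

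**Simulation of the stated regression sequence.** N = 500 without dropout; five true predictors at odds ratio 1.5 per SD, the rest noise; univariate screen at p < 0.05, then a logistic model. Optimism = apparent AUC − AUC in new patients.

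| Event rate | Candidates | Apparent | New patients | Optimism |
|---|---|---|---|---|
| 20% | 20 | 0.736 | 0.704 | 0.032 |
| 20% | 40 | 0.747 | 0.696 | 0.051 |
| 10% | 20 | 0.741 | 0.676 | 0.065 |
| 10% | 40 | 0.759 | 0.666 | 0.093 |
| 5% | 20 | 0.757 | 0.639 | 0.118 |
| 5% | 40 | 0.789 | 0.630 | 0.159 |

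A second run with 40 candidates (60 data sets per rate, 4000 new patients) gave 0.746 − 0.696 = 0.050, 0.760 − 0.674 = 0.086 and 0.801 − 0.634 = 0.167. A separate simulation had 29 candidates with pairwise correlation 0.2, odds ratios 1.5, 1.3 and 1.3, and 10% or 20% events. It gave 0.70–0.71 apparent against 0.64–0.65 in new patients.

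**If the ROC curve is for one marker only.** Best of 40 markers, apparent against new patients, at 20%, 10% and 5% events:

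- 0.642 − 0.599 = 0.043
- 0.655 − 0.608 = 0.047
- 0.690 − 0.579 = 0.111

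**No true signal, 40 candidates.** The screened logistic model shows an apparent AUC of about 0.60 to 0.70, against 0.50 in new patients.

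**Does the remedy work?** Five-fold cross-validation with the screen repeated in each fold gave 0.683, 0.656 and 0.626 at 20%, 10% and 5% events. The true values were 0.696, 0.674 and 0.634, so the estimates are close and slightly low.

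**XGBoost, conditional only.** With 100 trees of depth 3 and learning rate 0.1, the AUC on its own training patients was 1.00. In new patients it was 0.63, 0.62 and 0.60, and cross-validation gave 0.61, 0.60 and 0.61.

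**The case against.** The strongest reply is that this is a condensed article. Fold counts, tuning and bootstrap details are commonly left to a full protocol or analysis plan, and silence on them is not an error. That stands: a reader might infer that no resampling will be done, but the article nowhere says so.

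A reader might also infer that XGBoost will be graded on its training patients and will show an AUC near 1.00. The text does not support this. The ROC sentence follows the regression models, XGBoost appears in a different section, and nothing connects the two or gives the settings. Nor do the documents support the inference that a worthless new model would beat GRACE. The article states no AUC contest with GRACE, its test of incremental value is a likelihood ratio test over baseline models, and a screened regression on pure noise reached only about 0.60–0.70.

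Finally, section 5 limits the claim by asking for confirmation elsewhere. That is a fair caveat, but it does not correct the figures this study will report.

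What survives is the part that the article does state. The selection rule and the ROC assessment of what it yields are positive choices, and only one cohort is available for both. That goes beyond missing detail.

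**Conclusion.** The point holds for the regression-based analysis. Carried out as written, section 3.2 gives optimistic sensitivity, specificity and AUC for the markers and models that serve the study's main goal. The excess in AUC is about 0.03–0.05 at 20% events, 0.07–0.09 at 10% and 0.12–0.17 at 5%. At the 20% rate that reproduces the sample size it is moderate, though it could still be mistaken for a real increment.

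These sizes rest on assumed event rates, 20 to 40 candidates, five true predictors and a logistic model; Cox models were not simulated. Full follow-up of 500 was also assumed. Fewer events, from dropout, the STEMI and NSTEMI subgroups or early mortality, would tend to widen the gap.

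For XGBoost the conclusion is conditional: optimism would be very large if the model were scored on its training data, which the article does not say.

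**What to change.** Add to section 3.2, before outcomes are analysed:

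- Discrimination, sensitivity, specificity and calibration are reported as optimism-corrected estimates, by bootstrap for the regression models and nested cross-validation for XGBoost.
- Every data-driven step (univariate screening, tuning, any choice of cut-off) is repeated inside each resample.
- Any comparison with existing scores such as GRACE uses the optimism-corrected or out-of-sample predictions.

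I would not go further and fix Kaplan–Meier groups at the published 86% work efficiency and 750 mmHg% work index. Section 4 reports both from STEMI patients only, and this study also enrols NSTEMI.

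The cost is computing time, a few sentences and lower reported AUCs. No further patients or measurements are needed.

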## Abstract

Background: Acute myocardial infarction (AMI) remains a major cause of death worldwide. Survivors of AMI are particularly at high risk for additional cardiovascular events. Consequently, a comprehensive approach to secondary prevention is necessary to mitigate the occurrence of downstream complications. This may be achieved through a multiparametric tailored risk stratification by incorporating clinical, laboratory and echocardiographic parameters. Methods: The ‘‘CLEAR-AMI Study’’ (ClinicalTrials.gov Identifier: NCT05791916) is a non-interventional, prospective study including consecutive patients with AMI without a known history of coronary artery disease. All patients satisfying these inclusion criteria are enrolled in the present study. The rationale of this study is to refine risk stratification by using clinical, laboratory and novel echocardiographic biomarkers. All the patients undergo a comprehensive transthoracic echocardiographic assessment, including strain and myocardial work analysis of the left and right heart chambers, within 48 h of admission after coronary angiography. Their laboratory profile focusing on systemic inflammation is captured during the first 24 h upon admission, and their demographic characteristics, past medical history, and therapeutic management are recorded. The angioplasty details are documented, the non-culprit coronary lesions are archived, and the SYNTAX score is employed to evaluate the complexity of coronary artery disease. A 24-month follow-up period will be recorded for all patients recruited. Conclusion: The ‘‘CLEAR-AMI” study is an ongoing prospective registry endeavoring to refine risk assessment in patients with AMI without a known history of coronary artery disease, by incorporating echocardiographic parameters, biochemical indices, and clinical and coronary characteristics in the acute phase of AMI.

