## 3. Data Collection and Study Procedures

Demographic characteristics, baseline medical history, medication, prior diagnostic and therapeutic interventions, and clinical presentation of hospitalization will be recorded for all patients. In addition, patient laboratory data including complete blood count, biochemical, hormonal and coagulation mechanism control, high sensitivity troponin T levels (hs-cTNT) (admission and peak values) and N-terminal pro-B-type natriuretic peptide values will be collected within 24 h upon admission and during hospitalization. Moreover, the traditional lipid profile of the participants will be collected in addition to Lipoprotein A, and apolipoproteins B and A1. Special emphasis is placed on the assessment of inflammatory markers, including high-sensitivity C-reactive protein (hs-CRP), neutrophil-to-lymphocyte ratio (NLR), interleukin-6 (IL-6), soluble urokinase plasminogen activator receptor (suPAR), and admission glucose value, in order to evaluate stress-induced hyperglycemia. The prognostic impact of the investigated inflammatory markers (hs-CRP, IL-6, SuPAR) will be adjusted for potential cofounding variables such as concomitant autoimmune diseases and acute nosocomial infections as appropriate.

Clinical characteristics and risk scores, including Killip Class, GRACE risk score, TIMI-STEMI and ΤΙΜΙ-NSTEMI will also be recorded. Additionally, the coronary angiography of eligible patients will be assessed by two independent experienced interventional cardiologists who will be blinded to the demographic and clinical patient features. Angiographic data such as lesion characteristics, SYNTAX score and coronary dominance will also be taken into consideration.

All the eligible patients with AMI will be invited to visit the hospital one month post-AMI for a stress ECG test using the treadmill test. The test will be performed while the patient is on medication to assess the drugs’ effectiveness, their exercise capacity, and the chronotropic competence.

The primary endpoint will be all-cause mortality. The secondary endpoints will include (i) cardiovascular mortality (ii) heart failure rehospitalization and (iii) a composite of cardiovascular mortality, non-fatal acute myocardial infarction, unplanned PCI and heart failure hospitalization.

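### Kaplan–Meier is not limited to all-cause mortality and no competing-risk handling is stated, so curves read as risk would overstate the secondary endpoints, chiefly heart failure rehospitalisation in high-mortality groups

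*Protocol article*

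**What the plan says.** Section 3 of the protocol article sets the endpoints. On the primary it says: "The primary endpoint will be all-cause mortality". On the others: "The secondary endpoints will include (i) cardiovascular mortality (ii) heart failure rehospitalization and (iii) a composite of cardiovascular mortality", the composite being completed by non-fatal infarction, unplanned PCI and heart failure hospitalisation. Among deaths, the composite therefore counts cardiovascular deaths only.

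Section 3.2 names three time-to-event methods. For predictors: "Univariable and multivariable logistic regression analyses, and Cox regression analyses will be applied to identify independent predictors at follow-up". For groups defined by echocardiographic or laboratory features, and to compare those groups: "a time-to-event analysis will be performed according to the Kaplan–Meier method. A log-rank test will be used to compare the event rates".

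The Kaplan–Meier sentence names no endpoint and excludes none. The article mentions no cumulative incidence function and no cause-specific or subdistribution model, and does not say what happens to patients who die of a cause outside the endpoint. On the horizon, the abstract states: "A 24-month follow-up period will be recorded for all patients recruited".

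**The concern.** Each secondary endpoint leaves out some or all deaths:

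| Endpoint | Deaths that compete with it |
|---|---|
| Heart failure rehospitalisation | Any death before rehospitalisation |
| Cardiovascular mortality | Non-cardiovascular death |
| Composite | Non-cardiovascular death before a component event |

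Kaplan–Meier censors these patients and treats them as if they could still have the event later. One minus Kaplan–Meier (1−KM) then describes a setting in which the competing death does not occur. It exceeds the proportion of patients who actually have the event whenever such deaths happen.

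This matters because the introduction sets the goal of a predictive model that picks out high-risk patients. A reader will take a group's event curve as that group's risk. For heart failure rehospitalisation there is also reason to expect the error to differ between groups. The discussion (section 4) cites two studies in which poorer myocardial work values went with higher all-cause mortality. The markers that may define the groups are thus reported to predict the competing event, and the gap between the curves would be widened.

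**Working it through.** **Inputs.** From the article: the endpoints, the named methods and the 24-month horizon. The article gives no event or death rates and no figure on this point to reproduce, so all rates below are assumptions, shown as a range.

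**Formula.** Let r₁ be the 24-month 1−KM risk of the event and r₂ the 24-month net risk of the competing death, with constant cause-specific hazards. With 24 months as the unit of time:

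- λ₁ = −ln(1 − r₁) and λ₂ = −ln(1 − r₂)
- cumulative incidence = λ₁/(λ₁ + λ₂) × [1 − exp(−(λ₁ + λ₂))]
- excess = r₁ − cumulative incidence

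**Worked case, r₁ = 25% and r₂ = 30%.** λ₁ = 0.2877, λ₂ = 0.3567, sum 0.6444. 1 − exp(−0.6444) = 1 − 0.75 × 0.70 = 0.475. Cumulative incidence = (0.2877/0.6444) × 0.475 = 0.212. The excess is 3.8 points and the ratio 0.25/0.212 = 1.18.

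**Heart failure rehospitalisation, any prior death competing**

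| Event / competing death | 1−KM | Cumulative incidence | Ratio |
|---|---|---|---|
| 5% / 3% | 5.0% | 4.9% | 1.02 |
| 8% / 5% | 8.0% | 7.8% | 1.03 |
| 10% / 8% | 10.0% | 9.6% | 1.04 |
| 20% / 20% | 20.0% | 18.0% | 1.11 |
| 25% / 30% | 25.0% | 21.2% | 1.18 |

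If the 25%/30% and 8%/5% rows are taken as a high-risk and a low-risk group, the Kaplan–Meier gap is 25.0 − 8.0 = 17.0 points and the cumulative-incidence gap is 21.2 − 7.8 = 13.4 points.

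**Cardiovascular death, non-cardiovascular death competing**

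| Event / competing death | 1−KM | Cumulative incidence | Ratio |
|---|---|---|---|
| 3% / 1% | 3.00% | 2.99% | 1.005 |
| 8% / 2% | 8.0% | 7.9% | 1.01 |
| 15% / 5% | 15.0% | 14.6% | 1.03 |
| 20% / 10% | 20.0% | 19.0% | 1.05 |

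**Composite, non-cardiovascular death competing.** 10%/1% gives 10.0% against 9.95%; 35%/5% gives 35.0% against 34.2%.

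**Does the error grow with cardiovascular risk alone?** With non-cardiovascular death held at 2% in every group, the ratio stays near 1.01 for cardiovascular-death risks from 3% to 25%. The absolute excess rises only from 0.03 to 0.24 points.

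**Sensitivity of the largest case.** Only death before rehospitalisation competes, so using total mortality as r₂ can overstate the effect. Suppose total death is 30% and the death hazard triples after rehospitalisation (an assumption). The net risk of death before rehospitalisation is then about 25%, the cumulative incidence 21.8%, and the ratio 1.14 instead of 1.18.

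**The case against.** The strongest reply has five parts.

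1. **Kaplan–Meier is not assigned to these endpoints.** This is true: the sentence names no endpoint, and for the primary it is the right method. But the sentence is unrestricted, and the same section lists rehospitalisation among the outcomes to be predicted. Followed as written, it covers the secondary endpoints.
2. **A reader might infer that Kaplan–Meier and log-rank are the only time-to-event methods planned, or that the group comparisons are invalid.** The article supports neither reading. It names Cox regression in the same section. Log-rank and Cox with competing deaths censored validly compare cause-specific hazards. Gray's test answers a different question and is not a necessary replacement.
3. **A reader might infer that every predicted 24-month risk would be too high.** That does not follow. Logistic regression, or XGBoost used as a classifier, with status known at 24 months counts a patient who dies first as a non-event and so targets the actual risk.
4. **A reader might infer that high-risk groups are worst affected for all three endpoints.** This is supported only for heart failure rehospitalisation. For cardiovascular death and the composite it would need higher non-cardiovascular mortality in those groups, which the article does not show.
5. **The article is condensed, and the full protocol or analysis plan may deal with competing deaths.** This stands as a limit: silence alone would not be a point. The point rests on what the article does fix, which is an unrestricted choice of Kaplan–Meier for group prognosis.

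It is also fair to say that excluding patients with a life expectancy under one year (Table 1) lowers competing death, though it does not remove it over 24 months.

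**Conclusion.** The point holds in a limited form. As worded, section 3.2 leads to Kaplan–Meier curves for three endpoints that omit some or all deaths, and those curves read as risk would be too high. The direction is certain wherever competing deaths occur. The size is not, because every rate used is assumed and hazards are taken as constant.

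Over the range tried, the excess is about 0.1 to 4 points for heart failure rehospitalisation, with the top of that range needing 30% competing death. It is at most about 1 point for cardiovascular death and below 1 point for the composite. The practical concern is therefore heart failure rehospitalisation in groups with high mortality. This merits a correction to the wording but does not threaten the primary analysis.

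**What to change.** In section 3.2, or in the full plan if it carries the same wording:

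- Keep Kaplan–Meier for all-cause mortality.
- For cardiovascular mortality, heart failure rehospitalisation and the composite, report Aalen–Johansen cumulative incidence, with deaths outside the endpoint as the competing event.
- Keep log-rank and Cox for these endpoints and label them as cause-specific comparisons. Gray's test is optional.
- Where absolute 24-month risks are predicted from time-to-event models, use combined cause-specific models or a Fine–Gray model.

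The cost is a few sentences and a minor extra analysis. R is already planned, and the endpoints and time-to-event analyses already require the date and cause of death. The only downside is that the reported risks for these endpoints will be slightly lower.
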